### Strategies to improve adherence to intervention/comparator {15c}

Adherence to the allocated intervention or comparator is promoted through a combination of participant education, regular follow-up, and monitoring procedures. Patient adherence to the study intervention is assessed using three different methods, described below in the “Intervention and comparator”section; the RheumaBuddy mobile application, a paper-based questionnaire (BAASIS-MTX), and the measurement of biomarkers.

### Concomitant care permitted or prohibited during the trial {15d}

All participants will receive an open-label short-term GC pulse at baseline according to standard of care for active RA on MTX. The prednisone-equivalent dose and a standardised tapering scheme will be prescribed by the investigator and initiated on day 1 after baseline. GC intake during the first 4 weeks will be recorded in a patient diary. GC use beyond the initial taper will be documented at each visit.

Folate supplementation will be prescribed as standard of care for MTX therapy according to a predefined scheme and recorded as concomitant medication.

Permitted concomitant medications.TNFα inhibitors (stable ≥ 4 months)csDMARDs (stable ≥ 4 months)NSAIDs and analgesics at investigator’s discretion

Prohibited concomitant medications.

Initiation or dose escalation of immunomodulatory therapies. Introduction of additional cs/b/tsDMARDs, or other immunosuppressants will lead to discontinuation of the investigational product.

Participants will be instructed not to initiate any new medication without prior consultation with the investigator.

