## Methods: patient and public involvement, and trial design

### Patient and public involvement {11}

The study aims to enrol 182 patients across 7 European countries, at 7 study sites. Eligible patients need to be classified as having RA based on the ACR/EULAR 2010 classification criteria [30] with ongoing stable oral MTX therapy at a dosage of at least 10 mg/week to a maximum of 25 mg/week for at least 12 weeks. For inclusion, patients need to have active disease as assessed by the CDAI of > 2.8 AND at least one or more clinically swollen joints on a 28-joint count. History of any csDMARD and TNFi and their concomitant use in a stable dosing regimen is allowed. Concomitant treatment with glucocorticoids and non-steroidal anti-inflammatory drugs (NSAIDs) in a stable dosing regimen is allowed as described below.

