The exclusion criteria are as follows:Inflammatory rheumatic diseases other than RA.Ongoing or previous therapy with any targeted synthetic DMARDs (tsDMARD) or biological Disease-Modifying Anti-Rheumatic Drug (bDMARD) with the exception of any TNFα inhibitor in a stable dose and interval for at least 4 months. We allow ongoing or previous therapy with a conventional synthetic DMARD (csDMARD) with a stable dose in the past 4 months.Use of glucocorticoids (GC) unless on stable oral dose ≤ 10 mg for at least 4 weeks prior to study inclusion.Patients using NSAIDs, unless taken at a stable dose for ≥ 2 weeks prior to study inclusion.Intraarticular GC treatment in the last 8 weeks.Patients with significant and clinically relevant MTX-drug toxicity as judged by the investigator.Elevated liver enzymes (aspartate transaminase (AST) and/or alanine transaminase (ALT)), and/or alkaline phosphatase (AP), and/or gamma-glutamyl transferase (GGT) above two times the upper limit normal (ULN).Reduced kidney function (glomerular filtration rate (GFR) < 60 mL/min/1.73 m^2^).Haematologic abnormalities (grade 2 or 3: anaemia, leukopenia, thrombocytopenia).Stomatitis under treatment with MTX.Known history of recurrent/serious infections in the previous 2 months (such as, but not limited to, hepatitis, pneumonia, or pyelonephritis).A positive HBs antigen and/or hepatitis C virus (HCV) test at screening visit.Ongoing or recurring opportunistic infections (e.g. herpes zoster, cytomegalovirus, pneumocystis, aspergillosis, histoplasmosis, or mycobacteria) as judged by the investigator.Women of childbearing potential without the use of adequate birth control measures (e.g. abstinence, oral contraceptives, intrauterine device, barrier method with spermicide, implantable or injectable contraceptives or surgical sterilisation) and willing to continue this precaution for the duration of the study until 6 months after receiving the last medication.Current signs or symptoms of severe, progressive or uncontrolled renal, hepatic, haematologic, gastrointestinal, endocrine, pulmonary, cardiac, neurologic, or cerebral disease, as judged by the investigator.Being unable or unwilling to undergo multiple venipunctures because of poor tolerability or lack of sufficient venous access.Being unwilling or unable to perform s.c. injections.Presence of a transplanted solid organ (except for a corneal transplant > 3 months prior to screening).Women who are pregnant, nursing or planning pregnancy during the study and 6 months after the individual study completion.History of alcohol or substance abuse within the preceding 6 months.Any medical or psychological condition that, judged by the investigator, would interfere with the safe completion of the trial.Immunisation with a live/attenuated vaccine within 12 weeks prior to baseline or potential need to receive a live vaccine during the course of the study.Active participation in any other interventional study.

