### Criteria for discontinuing or modifying allocated intervention/comparator {15b}

Criteria for discontinuation or modification of the allocated intervention or comparator include safety concerns, serious or persistent adverse events, pregnancy, protocol deviations affecting participant safety, or investigator judgement. Participants may withdraw consent at any time without consequences for further treatment or study participation.

In case of a worsening of disease activity (CDAI increase > 4.5 compared to baseline) at each visit from week 4 onwards or inadequate improvement of the sum of swollen and tender joints (< 20% change compared to baseline) from week 12 onwards, rescue treatment applies according to standard of care (such as switch or add on of conventional synthetic, biologic or targeted synthetic DMARD (cs/b/tsDMARD)). This results in the participant’s early termination from the study. Non-responder imputation will apply to all patients with a premature end of study.

In case of an AE, a diagnostic or therapeutic procedure, an abnormal assessment (e.g. laboratory abnormalities) the MTX dose can be temporarily interrupted or reduced to ≥ 10 mg/week and re-escalated to 25 mg after resolution of the problem. If drug interruption or intermittent reduction is within a timeframe of ≤ 3 weeks, and re-institution of full dose of the study drug is safe according to the decision of the investigator, no permanent study discontinuation is required.

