**Exploratory endpoints**	
TDM in blood	Association of MTX-PGs levels and CDAI response at week 12 and week 24
	Association of MTX dosage, MTX-PGs levels and TTV titre as a potential marker to guide levels of immunosuppressive therapy at week 12 and week 24
Sweat analysis	Association between treatment-associated biomarker profiles and longitudinal clinical outcomes
GC dose	Difference in cumulative GC dose between treatment arms
Treatment adherence	Association of CDAI response and treatment adherence as measured by paper-based questionnaires, MTX metabolites and electronic adherence monitoring (in patients using the RheumaBuddy mobile app)
Safety parameters	Differences in safety profile according to number of AEs and organ systems (haematologic, hepatic, gastrointestinal, infections)
Disease trajectory	Trajectories of disease activity in the two groups over all visits, and its relation to predictors

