**Fig. 1 Fig1:**
[figure not shown]
Study flow chart, providing overview of the main inclusion/exclusion criteria, study assignment, efficacy assessments and main outcomes

**Table 2 Tab2:** Visit and assessment schedule (SPIRIT figure) according to the protocol version 2.0. Detailed description of laboratory parameters is found in section Data collection

Allowed visit window ± 7 days	**Screening (week-2)**	Baseline visit week 0	Visit week 4	**Visit week 12**	Visit week 16	**Visit week 24**
Written Informed Consent	**x**					
Demography and medical history	**x**					
Record RA classification criteria	**x**					
Inclusion/Exclusion Criteria	**x**	**x**				
Randomisation		**x**				
Distribution of study drug		**x**	**x**	**x**	**x**	
Concomitant Medications	**x**	**x**	**x**	**x**	**x**	**x**
Optional informed consent for electronic adherence (RheumaBuddy App)	**x**					

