### Sequence generation: type of randomisation {21b}

Patients are randomised in a 1:1 ratio, using stratified randomisation by study centre. Details of the software’s randomisation algorithm and any blocking to reduce predictability are documented internally and are not accessible to personnel enrolling participants or assigning interventions.

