## Assignment of interventions: blinding

### Who will be blinded {24a}

Joint assessors performing outcome measurements are blinded to participants’ study assignments. Patients, care providers and personnel performing randomisation are not blinded.

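### NSAIDs must be stable at entry, but on study they are left to an unblinded investigator with no stability condition: a cheap gap to close, of low to modest importance

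*Protocol article*

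**What the plan says.** **At entry.** The exclusion criteria in section {14a} of the Protocol article rule out "Patients using NSAIDs, unless taken at a stable dose for ≥ 2 weeks prior to study inclusion". Section {11} summarises eligibility and says that concomitant treatment with glucocorticoids and "non-steroidal anti-inflammatory drugs (NSAIDs) in a stable dosing regimen is allowed as described below".

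**On study.** Section {15d} lists permitted co-medication. The TNF inhibitor and csDMARD items each carry a condition of at least 4 months' stability. The third item reads "NSAIDs and analgesics at investigator’s discretion" and carries none. The prohibited list covers immunomodulatory and immunosuppressive drugs only. Patients are told to consult the investigator before starting any new medicine.

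**Blinding.** Section {24a}: "Patients, care providers and personnel performing randomisation are not blinded". Only the joint assessors are blinded.

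**Analysis.** Section {15b}: "Non-responder imputation will apply to all patients with a premature end of study". Sections {27b} and {27c} apply the same imputation to discontinuation and loss to follow-up, and {27c} plans no other imputation.

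**Data and reporting.** The "Concomitant Medications" row of Table 2 is ticked at every visit, and section {25a} names NSAIDs in the medication history. Among the endpoints in Table 1, one co-medication is compared by arm: "Difference in cumulative GC dose between treatment arms".

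**The concern.** Requiring a stable NSAID dose at entry keeps symptomatic treatment from being mistaken for an effect of methotrexate. Once allocation is known, the on-study rule drops that condition, and the person who decides knows the arm.

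The primary endpoint is CDAI ≤ 2.8 at week 24. Under standard scoring (an assumption, since the article gives no formula) it includes tender joints and the patient's global assessment, and an NSAID or analgesic can lower both. Blinded joint counts limit assessor bias. They do not undo a real fall in tenderness caused by a drug. Entry needs only CDAI above 2.8 and one swollen joint, so some patients may start near the cut-off, where a small shift changes the classification.

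A patient whose NSAID was started or increased and who reaches the cut-off counts as a remitter. If such changes differ by arm, part of the observed difference would reflect symptomatic treatment and not the route of methotrexate.

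**Working it through.** **1. The rules side by side**

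| Co-medication | Entry | On study | By-arm endpoint in Table 1 |
|---|---|---|---|
| TNF inhibitor, csDMARD | stable 4 months | stable 4 months; starting or escalating prohibited | none named |
| Glucocorticoid | stable, ≤ 10 mg, 4 weeks | fixed taper to zero or baseline dose; later use documented | cumulative dose |
| NSAID | stable 2 weeks | investigator's discretion | none named |
| Other analgesic | no condition stated | investigator's discretion | none named |

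A post-randomisation NSAID change is therefore permitted. It does not end participation, so it does not trigger imputation. The patient probably stays in the per-protocol set too, since a permitted drug is hardly a major violation. That is an inference, because section {27b} defines violations only in general terms.

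**2. The plan's sample size**

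Inputs from section {19}: 5% vs 20%, two-sided alpha 0.05, power 80%, 16% dropout, 1:1.

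n = [1.960·√(2·0.125·0.875) + 0.842·√(0.05·0.95 + 0.20·0.80)]² / 0.15² = (0.917 + 0.383)² / 0.0225 ≈ 75.1, so 76 per group. Then 76/0.84 = 90.5, so 91 per arm and 182 in total. Both stated figures reproduce.

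**3. Baseline for a stress test**

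With dropouts counted as failures, remission is 0.05 × 0.84 = 4.2% and 0.20 × 0.84 = 16.8% of 91, about 3.8 and 15.3 expected remitters. I summed the two binomial distributions over all outcomes, using the test rule of section {27a} (Fisher if fewer than five events in either group, otherwise uncorrected χ², two-sided 0.05). Power is 80.0%, in line with the plan. Ignoring dropout (5% vs 20% of 91) gives 88.6%, which is not the planned figure, so I do not start from it.

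**4. Stress test**

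The documents give no rate of NSAID starts, no NSAID effect on CDAI and no arm difference. The shifts below are assumptions and would apply to any co-intervention. Each extra remitter adds 1/91 = 1.1 percentage points to that arm's rate.

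| Extra remitters | Power (4.2% vs 16.8%) |
|---|---|
| none | 80.0% |
| 1 / 2 / 3 in each arm | 77.0% / 73.8% / 70.7% |
| 1 / 2 / 3 oral only | 70.1% / 59.3% / 48.3% |
| 3 oral, 1 s.c. | 56.3% |

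| Extra remitters, no true effect (4.2% in both arms) | Two-sided rejection rate |
|---|---|
| none | 1.6% |
| 2 in each arm | 2.5% |
| 1 / 2 / 3 s.c. only | 2.5% / 4.9% / 9.0% |
| 3 s.c., 1 oral | 5.2% |

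Two extra in each arm cost 80.0 − 73.8 = 6.2 points of power. A net excess of two in the oral arm costs 80.0 − 59.3 = 20.7 points, or 80.0 − 56.3 = 23.7 points when it arises as three against one. A net excess of two in the s.c. arm leaves the false-positive rate near 5%. Net imbalance is what matters most.

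**The case against.** The case for leaving the rule alone is substantial.

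- **Discretion is a legitimate choice.** This is a Phase IV low-intervention trial, and entry criteria and on-study care serve different purposes. A reader might infer that sections {11}, {14a} and {15d} contradict each other. They do not: the first two concern entry, and {11} refers onward to later text. Equally, {11} does not supply the missing on-study condition.
- **Handling is defined by default.** A reader might infer that the plan has no way to treat these patients. In effect it has a treatment-policy approach: they are analysed as allocated and as observed. Only an NSAID-specific rule is absent, and a sensitivity analysis or by-arm medication table may be in the analysis plan, which is not shown.
- **Safeguards exist.** Joint counts are blinded. Worsening of CDAI by more than 4.5, or less than 20% joint improvement from week 12, leads to exit as a non-responder. New medicines require consultation. Section {15b} thus removes many clear failures, though not a patient near the cut-off, and the investigator consulted may know the arm. The Discussion discloses the lack of blinding.
- **The figures say nothing about NSAIDs.** This stands in full. A reader might take the tables as showing that the primary result is biased or that power is lost. They show only how sensitive a comparison with few events is to a small net imbalance from any source.
- **The same investigator still decides under a clinical-need exception.** This is partly right. The default changes from free choice to no change, and departures become visible by arm.

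What remains is that section {15d} itself fixes a looser rule for NSAIDs than for the drugs listed beside it, on an endpoint that such drugs can move, under open allocation.

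**Conclusion.** The point holds as a cheap improvement of low to modest importance. The stability condition set at entry is not carried into the on-study rule, and a start or increase after open allocation is analysed as observed.

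The size and direction of any bias cannot be derived from the documents. Similar use would largely cancel. More use in a less effective oral arm would work against superiority; more use in the s.c. arm would work towards it. The illustration (80.0% to about 59% with two extra oral remitters) rests on assumed shifts and on all 16% dropouts counting as failures. The mechanism rests on standard CDAI scoring. No error in the primary analysis is shown, and none should be inferred.

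**What to change.** 1. **Conduct rule.** In section {15d}, replace the NSAID item with: NSAIDs and regular analgesics stay at the baseline dose through week 24 unless a change is clinically needed; the drug, dose, dates and indication of any start or increase are recorded.
2. **Reporting.** Report starts and increases by arm, as is planned for cumulative glucocorticoid dose.
3. **Supportive analysis, if the analysis plan does not already have one.** Repeat the primary comparison in the same modified ITT set with the same χ²/Fisher rule. Count as non-responders all patients with any NSAID or regular analgesic started or increased after randomisation and ongoing at week 24. Do this regardless of indication, because unblinded staff assign the indication. The primary analysis is unchanged.

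**Cost.** One line, best bundled with the next amendment, since version 2.0 was approved only in August 2025. Enrolment is planned to November 2026, so later patients would benefit. Some patients will have been treated under the present rule, but "Patients are randomised in a 1:1 ratio, using stratified randomisation by study centre", so the two arms should be spread similarly over both periods. Concomitant medication is already recorded at each visit; the article does not say that indication is, so that field may be new. Investigators lose a little prescribing freedom. Remission rates in the supportive analysis will be somewhat lower, and it will count as failures some patients treated for unrelated complaints.

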### Ancillary and post-trial care {34}

A voluntary follow-up visit occurs 4 weeks after premature discontinuation of the study drug, during which clinical disease activity and relevant laboratory safety and inflammatory parameters are assessed. After completion of the trial, participants return to routine standard-of-care follow-up.

## Outcomes {16}

The detailed description of primary, secondary and explorative endpoints is provided in Table 1.

**Table 1 Tab1:** Endpoints and definitions

Endpoint	Definition
**Primary endpoint**	
CDAI remission at week 24	Achievement of remission defined as the Clinical Disease Activity Index (CDAI) ≤ 2.8 assessed 24 weeks after randomisation comparing patients with dose/route optimisation and oral dose optimisation
**Secondary endpoints**	
CDAI activity and ACR response at different timepoints	To assess the proportion of patients: -In CDAI low disease activity (≤ 10) at weeks 24 and 12 -In CDAI remission (≤ 2.8) at week 12 -Achieving an ACR20, ACR50, ACR70 response at week 24 and 12 respectively
Patient reported outcomes	Difference in change (absolute and relative) of patient reported outcomes, including pain, patient global assessment, FACIT-F, SF36v1 and HAQ-DI between the treatment groups between baseline and week 24 and 12 respectively
Clinical and laboratory disease markers	Difference in change (absolute and relative) of swollen joint count, tender joint count, and C-reactive protein (CRP)/erythrocyte sedimentation rate (ESR) at week 24 between the treatment groups between baseline and week 24 and 12 respectively

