## Eligibility criteria for participants {14a}

The inclusion criteria are as follows:Men and women, ≥ 18 years of age, capable of understanding and signing an informed consent (including sufficient literacy and proficiency in the local language) and following the study procedures.Patients with RA according to the 2010 ACR/EULAR classification criteria.Ongoing conventional therapy with oral MTX (between ≥ 10 mg and 25 mg weekly) for ≥ 3 months with stable dosing, and clinical and laboratory tolerance of this treatment for at least 12 weeks.CDAI > 2.8 + at least 1 clinically swollen joint (on 28-joint count).Willingness to increase MTX dosing and change the route of administration according to study procedures.

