## Statistical methods

### Statistical methods for primary and secondary outcomes {27a}

The null hypothesis is as follows: The use of 25 mg SCMTX is not superior to 25 mg POMTX weekly in patients with active RA, previously treated with POMTX.

The primary endpoint, defined as the proportion of patients achieving CDAI remission at week 24, will be compared between treatment groups using a *χ*^2^ test. A Fisher’s exact test will be used if the endpoint occurs in fewer than five patients in any group. Superiority of the subcutaneous MTX arm will be tested at a two-sided alpha level of 0.05.

Secondary categorical outcomes will be analysed using *χ*^2^ tests (or Fisher’s exact tests where appropriate), and non-normally distributed continuous outcomes will be analysed using the Mann–Whitney *U* test. For categorical variables, absolute frequencies and percentages will be reported. Time to CDAI remission will be analysed using Kaplan–Meier curves, reporting medians and interquartile ranges, and compared between treatment groups using a log-rank test.

Secondary endpoints will be tested in a pre-specified stepwise hierarchical order until the first non-significant result is reached. All outcomes tested thereafter will be considered exploratory (hypothesis-generating). The following sequence for secondary endpoint testing will be utilised: Proportion of CDAI remission at week 12 > CDAI low disease activity (≤ 10) at week 24 > CDAI low disease activity (≤ 10) at week 12 > ACR70% response at week 24 > ACR50% response at week 24 > Difference in change of patient global assessment > HAQ-DI > CRP at week 24 respectively. An early analysis of the main secondary endpoints will be performed at week 12. All other secondary outcomes will be analysed exploratorily.

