Overall, the strength of the MethMax trial lies in its study design and procedures, combining multiple objective and subjective measurements of disease activity, patient outcomes and treatment adherence. The efforts to maximise the therapy adherence should deliver more representative results on the true pharmacological effects of MTX in its distinct routes. The main limitations of this study could include recruitment problems due to the relatively stringent inclusion/exclusion criteria, reliance on self-reported and self-performed data, and the impact of daily variations of subjective disease activity, especially in patients with an initial low disease activity score. Furthermore, patients and physicians are unblinded to the treatment allocation, and only joint assessment is performed by blinded personnel.

The anticipated results might bring valuable knowledge about the “maximisation” of the MTX therapy potential in patients with RA, providing recommendations on the optimal dose and administration route.

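### Patients entering with CDAI above 2.8 and up to 10 already meet the low-disease-activity endpoint, which is ranked second and third and tested without regard to baseline

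*Protocol article*

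**What the plan says.** **Entry.** The eligibility criteria {14a} require "CDAI > 2.8 + at least 1 clinically swollen joint (on 28-joint count"; section {11} repeats this. Neither sets a lower limit above 10.

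**Endpoint.** The secondary endpoint in Table 1 begins "To assess the proportion of patients: -In CDAI low disease activity", and the full item reads "In CDAI low disease activity (≤ 10) at weeks 24 and 12". This is a state at a visit, with no change from baseline required.

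**Test and rank.** Section {27a} applies a χ² test (or Fisher's exact test) to secondary categorical outcomes. After CDAI remission at week 12 the sequence runs "CDAI low disease activity (≤ 10) at week 24 > CDAI low disease activity (≤ 10) at week 12", followed by ACR70, ACR50, patient global assessment, HAQ-DI and CRP. Confirmatory testing stops at the first non-significant result.

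**Patients concerned.** The Discussion lists daily variation in subjective disease activity as a limitation, "especially in patients with an initial low disease activity score", so the authors expect some such patients. Their share is not given.

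**Rescue and imputation.** Under section {15b}, a joint-count change below 20% from week 12 onwards, or a CDAI rise above 4.5 from week 4 onwards, leads to rescue and early termination, with non-responder imputation for every premature end of study. Section {27b} also imputes non-response for patients who discontinue, without naming an endpoint. Section {27c} states the imputation for the primary endpoint and plans no other method.

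**The concern.** The entry rule protects the remission endpoints, because nobody enters at CDAI ≤ 2.8. It gives no such protection at the cut-off of 10. A patient who enters at CDAI 8 is in low disease activity on day 0, and the objectives {10} speak of patients achieving that state.

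If these patients do about equally well in both arms, they pull the two proportions together. A smaller difference at ranks 2 and 3 makes it more likely that the sequence stops there, which would leave the five endpoints behind them exploratory. The reported proportion in low disease activity would also mix patients who reached the state with patients who never left it.

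**Working it through.** **1. The plan's own figure.** The article gives a sample size for the primary endpoint only: 5% vs 20%, two-sided alpha 0.05, power 80%. With pooled variance and no continuity correction:

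n = [1.96·√(2·0.125·0.875) + 0.8416·√(0.05·0.95 + 0.20·0.80)]² / 0.15² = (0.917 + 0.383)² / 0.0225 ≈ 75.1, so 76 per group.

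76 / 0.84 = 90.5, so 91 per arm and 182 in total. Both stated figures reproduce. No rate or power is given for low disease activity.

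**2. Does an unchanged patient with baseline CDAI ≤ 10 count as a success?**

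- *Week 12 (rank 3): yes.* The joint-count rule first applies at this visit, when the week-12 CDAI is already in hand. An unchanged CDAI does not trigger the other rescue rule.
- *Week 24 (rank 2): mostly no, under {15b} and {27b}.* A patient without joint improvement at week 12 or 16 is terminated and imputed as a non-responder. Exceptions are patients whose joint counts improve at weeks 12 and 16 and then return to baseline by week 24.
- *Week 24 if {27c} governs: unsettled.* Imputation would then be limited to the primary endpoint. The terminated patient would have no week-24 value and no rule for supplying one.

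**3. Effect on power.** Let f be the share entering at CDAI ≤ 10. The rate in each arm is f·q + (1 − f)·p, where q applies to patients entering at ≤ 10 and p to those entering above 10. Assumed, because the article gives none of these: p = 40% oral and 60% subcutaneous, 91 analysed per arm.

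Power = Φ{[d·√n − 1.96·√(2·p̄·(1 − p̄))] / √[a(1 − a) + b(1 − b)]}, with arm rates a and b, d = b − a, and p̄ their mean.

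Example with f = 30% and q = 85% in both arms:

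- a = 0.3·0.85 + 0.7·0.40 = 0.535
- b = 0.3·0.85 + 0.7·0.60 = 0.675
- d = 0.14, p̄ = 0.605
- Power = Φ[(0.14·9.539 − 1.96·0.691) / 0.684] = Φ(−0.03) ≈ 49%

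| q, oral vs s.c. | f = 20% | f = 30% | f = 40% |
|---|---|---|---|
| 85% vs 85% (no effect) | 59% | 49% | 39% |
| 75% vs 85% (10 points) | 69% | 65% | 61% |
| 65% vs 85% (20 points) | 78% | 78% | 79% |

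With f = 0 the power is 77%. The decisive assumption is the treatment effect within the low stratum. The common level of q matters little: at f = 30% with no effect there, lowering q from 85% to 40% leaves power at 47–49%. Another choice of p (30% vs 50%, q = 75% in both arms) gives the same pattern: 79% at f = 0 and 58/47/37% at f = 20/30/40%.

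**4. Alternatives.** Restricting the endpoint to baseline CDAI > 10, with 91(1 − f) per arm, gives 68/62/55% at f = 20/30/40%, whatever q is. A CMH test stratified by baseline CDAI ≤ 10 / > 10 was simulated at f = 30%. Against the unadjusted χ² in the same simulations, power was about 53% vs 50% (no effect in the low stratum), 69% vs 65% (10 points) and 81% vs 78% (20 points). These values are good to about one point.

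**The case against.** The strongest reply is that low disease activity is a recognised target state, and that comparing a state between randomised arms is valid whatever the baseline. This stands. Type I error is unaffected, the primary endpoint and its sample size are untouched, and a stop at rank 2 or 3 only makes later secondary endpoints exploratory. Rank 1, remission at week 12, is also unaffected.

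Second, the power loss is assumed rather than shown. This stands as well: the share and all rates are unknown, and with an equal 20-point effect in both strata nothing is lost.

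Third, adjustment for baseline is often left to the analysis plan, which is not shown. This carries less weight here, because the article itself fixes the endpoint, the unadjusted test, the ranks and the stopping rule.

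Four stronger readings are tempting, and the article does not support them:

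- A reader might infer that eligible patients in general meet the endpoint at entry. Only those with CDAI above 2.8 and up to 10 do.
- A reader might infer that standing still counts as success at both visits. At week 24 the rescue rule with non-responder imputation mostly rules this out, if the imputation applies.
- A reader might extend the fault to ACR50 and ACR70. These require improvement from baseline and cannot count non-change as success.
- A reader might conclude that the ranked endpoint should be restricted to baseline CDAI > 10. With a 10-point effect in the low stratum and a 30% share, restriction gives 62% against 65% for the present analysis, so it is a trade-off.

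**Conclusion.** The point holds in limited form. An unknown share of patients meets the low-disease-activity endpoint at randomisation, and the endpoint's rank and unadjusted test take no account of this. Non-change counts as success at week 12. At week 24 it mostly does not, unless {27c} limits the imputation to the primary endpoint, in which case the outcome of rescued patients is undefined.

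The consequence is a possible loss of power and a proportion that is harder to interpret. At a 30% share, power ranges from about 49% to 78%, depending on whether the low stratum shows no effect or a 20-point effect. This rests on the assumed 40% vs 60% above CDAI 10 and on 91 analysed per arm. The size is therefore conditional, whereas the overlap between entry range and endpoint, and the disagreement over imputation, follow from the text alone.

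**What to change.** 1. In {27a}, test low disease activity at weeks 12 and 24 with a CMH test stratified by baseline CDAI ≤ 10 / > 10, or with a model adjusted for baseline CDAI. Keep all patients in the analysis and leave the ranks as they are. The gain is modest (about 3 to 4 points of power in the simulations at a 30% share). It does not restore what a large unaffected stratum would dilute, but it matched or beat the χ² test in every scenario simulated.
2. Report by arm the share already at CDAI ≤ 10 at baseline. Give the results for patients with baseline CDAI > 10 as a supportive analysis outside the hierarchy, and list it in {27d}, which at present plans no formal subgroup analyses.
3. Reconcile {15b}, {27b} and {27c} on whether non-responder imputation covers the secondary responder endpoints.

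The cost is wording in the protocol and analysis plan, settled before the week-12 analysis. No patients or visits are added, because Table 2 already schedules the joint counts and both global assessments at baseline.
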